### 2.6. Randomisation

Participants are randomised (1:1:1) to the control group (WLC) or intervention groups (iEFT or iMMI) stratified by age (< or ≥50 years), chemotherapy (yes or no), and gender (male or female). The stratified randomisation will be performed at the local sites by the site PI or his/her designee using the randomisation module of REDCap. REDCap is a secure, web-based application designed to support data capture for research studies. The REDCap software (REDCap 14.3.0) will randomise patients based on the statistical method with random permuted blocks that will be created with a computer random number generator with variable sizes to avoid the treatment allocation being predicted [27].

After randomisation, participants will be unblinded to group assignment, as the interventions do not allow for blinding. For analysis, assessor(s) and statistician(s) will be blinded.

### 2.7. Interventions

The intervention will be remotely delivered through Microsoft Teams, as the Microsoft Office 365 package is sufficiently covered for all patient data privacy requirements by the coordinating site az groeninge (MS Teams complies with the provisions of the HIPAA Security Rule and GDPR privacy and security law). Participants will all be well-informed on the use of MS Teams before signing the ICF.

#### 2.7.1. Intervention Group—iEFT

Participants allocated to the iEFT group follow three iEFT sessions, individually guided by a clinical psychologist trained in EFT (EFT level 1 certificate acknowledged by EFT International [EFTi, Tiverton, United Kingdom]). During the trajectory, there is an in-depth initial session (±90 min) and two additional sessions (lasting ±45 and ±25 min, respectively). The duration of each session is stored in the electronic health record (i.e., measurement of time toxicity; Table 1). All sessions are guided by the iEFT practitioner on a 1:1 level.

During the first iEFT session, participants will be taught how to apply EFT and how it can be used as an application for mood and physical side effects. They will receive a digital information brochure including a section that illustrates the application of the tapping protocol. This visualisation of tapping points (Figure 2) and self-measurement scale serves as a tool to support and encourage home practice. Patients may indicate in the MyNexuzHealth app whether and when they have applied EFT. For participants who prefer a paper version of the ‘EFT diary’, it is allowed to print out the forms at home. This (digital) notebook containing a structured self-work outline will be consulted during the follow-up iEFT sessions to evaluate the previous weeks and one’s evolution throughout the iEFT trajectory.

Each session will give tools to the participants to facilitate their practice of EFT at home through formal EFT practice (together with the iEFT practitioner) as well as through guidance in the informal use of EFT during daily life. During each session, the iEFT practitioner will assist the participants in learning this practice and will regularly assess how the participants are doing with their EFT practice. An overview of the iEFT programme is presented in Appendix B.

#### 2.7.2. Active Control Group—iMMI

The specific curriculum for this 2 h/week, 6-week programme will be provided to cancer survivors who are assigned to this group as part of the randomisation. Each session will provide structured training and exercises in mindfulness, and cancer survivors will be given tools to facilitate their practice of these techniques at home through formal meditation practice as well as through guidance in the informal use of mindfulness during daily life. During each session, the instructor will assist the participants in learning this practice and will regularly assess how the participants are doing with their mindfulness practice. All sessions are guided by a clinical psychologist who is a certified mindfulness trainer. A detailed training manual is presented in Appendix B.

#### 2.7.3. Wait-List Control Group

The participants assigned to this group after randomisation will not receive any specific intervention until they have completed their T2 research assessment (12 weeks after the assignment to the WLC group). Hereafter, participants will be offered participation in the iEFT or iMMI programme after they have completed the assessments. The participants allocated to the wait-list may thus choose their preferred programme.

### 2.8. Measures

An overview of measures is given in Table 3 and Supplementary Materials Section SC (Table S3).

Participants may consent to deliver a hair sample at T0 and T1 to explore the effect of both interventions on chronic biological stress measured as hair cortisol concentration. For the analysis of the levels of cortisol in the hair samples, a separate protocol will be developed, and approval will need to be obtained from the ECs of all participating sites in the REMOTE trial. Analysis would take place in collaboration with the ARU biomarker laboratory (Cambridge, UK) [30]. The laboratory holds a Human Tissue Authority license and is the only Salimetrics (Carlsbad, CA, USA) approved centre of excellence for testing in the UK.

### 2.9. Analysis Plan

Primary outcome measures:The difference in mean scores from the baseline on the FCRI between the iEFT group and the WLC group at T1;The difference in mean scores from the baseline on the FCRI between the iMMI group and the WLC group at T1;

Secondary outcomes measures:Changes in emotional distress, QoL, and health status;The difference in mean scores from the baseline on the FCRI between the iMMI group and the WLC group;

Tertiary outcomes measures:Changes in the cortisol biomarker

### 2.10. Data Analysis

All planned analyses will be performed according to the intention-to-treat principle.

Descriptive statistics will be used to describe demographic and clinical characteristics.

Clinical and psychosocial outcomes will be compared between groups using linear mixed models. Linear mixed-effects models will assess whether the improvement in FCRI scores and secondary PROMs is significantly different over time. Models will explore time x group as an interaction effect and will include the stratification variables (age, chemotherapy, and gender). Estimated marginal means with 95% confidence interval (CI) will be calculated for each time point for both groups. A 5% significance level will be used.

Within-group differences will be calculated by pairwise comparisons, enabling us to detect differences over time within the three groups. Between-group differences in the primary outcome at the primary endpoint T1 will be further examined with pairwise comparisons with T0 as the reference time point. These analyses will be repeated for the secondary PROMS: distress, QoL, and health status.

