### 2.5. Sample Size Calculation

The sample size calculation takes into account the principle of minimization for randomization, with participants randomized into either the iEFT group, iMMI group, or WLC group. In order to achieve at least 80% power to detect a between-group difference in mean FCRI at T1 of 10 points using an independent samples *t*-test at the two-sided 2.5% significance level (two experimental groups are compared against a single control), a total sample size of 444 patients (148 in each group) is needed, assuming a common standard deviation for FCRI in all groups of 27.9 points.

When taking into account baseline FCRI as a covariate in the regression model, the calculated sample size can be reduced by a design factor equal to (1 – r^2^) [28]. Assuming a correlation between baseline and follow-up FCRI of 0.6, the sample size reduces to 288 patients in total. This sample size has been increased to 339 patients in total to allow for an expected drop-out rate of 15%. This means we will include 113 patients in each group: iEFT (intervention), iMMI (active control), and the WLC group.

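### Section 2.10 attaches its significance statement to the all-visit time x group model at 5% and leaves the two T1 contrasts with the wait-list, on which the trial is sized at 2.5% each, as a further step

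*Protocol article*

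**What the plan says.** Three sections of the protocol article agree on the primary question.

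- Section 2.1 gives two hypotheses: each programme improves FCR relative to the wait-list at T1.
- Section 2.9 lists the matching primary outcome measures: "The difference in mean scores from the baseline on the FCRI between the iEFT group and the WLC group at T1" and "The difference in mean scores from the baseline on the FCRI between the iMMI group and the WLC group at T1".
- Section 2.5 sizes the trial for one such contrast, with "at least 80% power to detect a between-group difference in mean FCRI at T1 of 10 points", tested "at the two-sided 2.5% significance level" because two arms share one control.

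Section 2.10 is framed differently. Its significance statement reads "Linear mixed-effects models will assess whether the improvement in FCRI scores and secondary PROMs is significantly different over time". The effect it names is time x group, and it sets a single 5% level. T1 comes in the next paragraph: "Between-group differences in the primary outcome at the primary endpoint T1 will be further examined with pairwise comparisons with T0 as the reference time point".

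Three other places bear on this. Table 3 schedules the FCRI at T0, T1, T2 and T3. Section 2.7.3 offers wait-list participants a programme once their T2 assessment is done. Table 1 makes iEFT versus iMMI a secondary objective, and its footnote makes the cortisol objective conditional on a positive primary objective.

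**The concern.** The overall time x group interaction is not the quantity in section 2.9. With three arms and four visits it has (3 - 1) x (4 - 1) = 6 degrees of freedom. It pools T1 with T2 and T3, it counts a difference between the two programmes as evidence, and it uses T3 data from controls who may by then have been treated.

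Two things are at stake. If an analyst takes the overall test as a gate to the T1 comparisons, each comparison loses power that section 2.5 did not allow for. If the overall test is taken as the primary result, a late effect or an improvement among controls after T2 can make the trial look positive with no T1 benefit. The level is also open: 2.5% per contrast in section 2.5, 5% in section 2.10.

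**Working it through.** **Reproducing the plan's sample size.** Inputs from section 2.5: difference 10, SD 27.9, two-sided alpha 0.025, power 0.80, correlation 0.6, drop-out 15%.

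- Unadjusted: n = 2 x (2.2414 + 0.8416)^2 x 27.9^2 / 10^2 = 147.98, so 148 per arm and 444 in total, as stated.
- Baseline adjustment: 444 x (1 - 0.6^2) = 284. The stated 288 (96 per arm) is what 150 per arm from an exact t-test gives: 450 x 0.64 = 288.
- Drop-out: 288 / 0.85 = 338.8, so 339 (113 per arm), as stated.

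**Power of one T1 contrast at 96 per arm.** Baseline-adjusted SE = sqrt(2 x 27.9^2 x 0.64 / 96) = 3.22. Then 10 / 3.22 = 3.104, and power = Phi(3.104 - 2.241) = 0.806. The stated N therefore belongs to the T1 contrasts at 2.5% each.

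**Comparing the T1 contrasts with the overall test.** Arm means were simulated (at least 200,000 trials per pattern) with 96 per arm and SD 27.9. The T1 contrasts were baseline-adjusted, at two-sided 2.5% each. The overall test was the 6-df Wald test of time x group over T0-T3 at 5%. Not in the document, and so assumed: a correlation of 0.6 between every pair of visits (section 2.5 gives it for baseline to follow-up only), known variance, and the effect patterns at T2 and T3.

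| True pattern | One T1 contrast | Same, if gated by overall test | Either T1 contrast | Overall test | T1 positive, overall not | Overall positive, no T1 contrast |
|---|---|---|---|---|---|---|
| Both programmes 10 better at T1-T3 | 81% | 73% | 92% | 85% | 10.7% | 4.4% |
| Both 10 better at T1-T2, benefit lost by T3 | 81% | 78% | 92% | 95% | 3.3% | 6.3% |
| No T1 effect, wait-list improves 10 at T3 | 2.5% | - | 4.7% | 85% | 0.2% | 81% |
| No effect anywhere | 2.5% | - | 4.6% | 5.1% | 3.3% | 3.8% |

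**The level.** With no true effect, the chance that at least one of the two T1 contrasts is significant is about 4.6% at 2.5% each and about 9.1% at 5% each.

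**Sensitivity to the estimator.** If the T1 contrast is a plain change from T0 without baseline adjustment, the SD of change is 27.9 x sqrt(2 x 0.4) = 24.95, the SE is 3.60 and single-contrast power is 70.4%. A gate then takes it to 66.6% in the first pattern. That lower starting point comes from the estimator and is not a consequence of the wording in section 2.10.

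**The case against.** A reader might infer that section 2.10 sets up a rival decision rule, so that the article holds two stated criteria that can give opposite conclusions. The text does not support that. Section 2.10 says the models will explore time x group, keeps T1 as the primary endpoint, and nowhere makes the interaction a gate or success criterion. The terms overall test and 6 degrees of freedom are this review's description, not the article's.

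There is also a consistent reading. In a time x group model with T0 as reference, the group-by-T1 term is the between-arm difference in change from baseline at T1, which is what section 2.9 asks for. One model can supply the planned contrasts, so the choice of model is not at fault.

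It can be added that test hierarchy is often left to the analysis plan, that the cortisol trigger is fairly clear from section 2.1, and that the simulated patterns are hypothetical. The gate loss is small if the benefit is gone by T3, and no passage predicts a 10-point wait-list improvement at T3.

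Most of this stands, and it limits the point to ambiguous wording. It does not remove the point. Section 2.10 is not silent: it says what is tested for significance and at what level, and as written neither matches sections 2.5 and 2.9. The sizes depend on the assumed T2 and T3 patterns; the mismatch does not.

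**Conclusion.** The concern holds in a limited form. The primary question is well defined in sections 2.1, 2.5 and 2.9, and the sample size fits it. Section 2.10 puts its significance statement on the over-time model at 5% and places T1 after it. That leaves room to treat the overall interaction as the deciding or gating test, although the article does not say that it is.

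Under the listed assumptions, a gate costs about 8 points of single-contrast power if the benefit persists through T3 and about 2 to 3 points if it is lost by T3. Read as the primary result, the overall test could be significant in about 85% of trials with no T1 effect if only the wait-list improved 10 points at T3; in about 81% there would be no significant T1 contrast at all. Testing the T1 contrasts at 5% each would give about 9% family-wise error. This should be settled before unblinding.

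**What to change.** In section 2.10, or in the analysis plan before unblinding:

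- State that the two model-based T1 contrasts with the wait-list, iEFT-WLC and iMMI-WLC, taken from the same mixed model with T0 as reference, are the only tests that decide the primary objective.
- Test each at two-sided 2.5%, as in section 2.5, whatever the overall interaction shows.
- Treat the overall time x group test and all T2 and T3 contrasts as supportive.
- Replace the wording that makes T1 a further step.
- Say that the T1 contrasts are baseline-adjusted, since the power in section 2.5 relies on it.

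This is a change of wording. Sample size, mixed model and data collection stay as they are, and the article reports 82 of 339 participants on 31 July 2025, so there is time. The only cost is that a significant overall interaction can no longer be presented as the primary result.

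### The sample size is cut by 36% for baseline adjustment, but the stated analysis compares change from T0 without that adjustment, so power is about 70% rather than 80%

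*Protocol article*

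**What the plan says.** Section 2.5 (Sample Size Calculation) aims for "at least 80% power to detect a between-group difference in mean FCRI at T1 of 10 points", tested "at the two-sided 2.5% significance level (two experimental groups are compared against a single control") and "assuming a common standard deviation for FCRI in all groups of 27.9 points". From this, "a total sample size of 444 patients (148 in each group) is needed". The next step reads: "When taking into account baseline FCRI as a covariate in the regression model, the calculated sample size can be reduced by a design factor" of 1 − r². With an assumed baseline-to-follow-up correlation of 0.6 the total falls to 288, and 15% drop-out brings it to 339, or 113 per arm.

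Section 2.9 (Analysis Plan) defines the first primary outcome measure as "The difference in mean scores from the baseline on the FCRI between the iEFT group and the WLC group at T1", with a parallel definition for iMMI against the wait-list.

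Section 2.10 (Data Analysis) specifies linear mixed models with a time by group interaction that "will include the stratification variables (age, chemotherapy, and gender"). Marginal means are estimated at each time point, and the between-group difference at T1 is examined by "pairwise comparisons with T0 as the reference time point". Baseline FCRI is not among the listed terms, and nothing says that the arms share a common T0 mean.

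**The concern.** The factor 1 − r² is the variance reduction from adjusting for baseline, either as a covariate or through a model that constrains the T0 means to be equal across arms. It does not apply to a difference in mean change. When T0 is a response with arm-specific means, the time by group contrast at T1 is exactly the difference in mean change from T0. Using a mixed model does not alter that, and the stratification variables, being constant over time, cancel from a T1-minus-T0 contrast.

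The sample size and the analysis section therefore describe different estimators, and the stated power belongs only to the first. The difference of 10 points is the one section 2.1 treats as clinically significant, so the plan carries a larger chance of missing it than it declares. Change scores also over-correct a chance baseline imbalance: with equal SDs and r = 0.6 they subtract the whole imbalance where regression would subtract 0.6 of it.

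**Working it through.** **Inputs (all from section 2.5).** Difference 10; SD 27.9 in all groups; two-sided α = 0.025 per comparison; power 80%; r = 0.6; drop-out 15%. Equal SD at T0 and T1 is taken from the common-SD assumption.

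**Reproducing the plan's figures.**
- Unadjusted, normal formula: n per arm = 2 × (2.2414 + 0.8416)² × (27.9/10)² = 147.98, so 148 per arm and 444 in total. This agrees with the protocol.
- Baseline factor: 1 − 0.6² = 0.64. Applied to 444 it gives 284.2. Applied to 150 per arm, the number an exact t-test needs, it gives 96 per arm, or 288. The protocol's 288 is therefore consistent with the exact t-test.
- Drop-out: 288/0.85 = 338.8, so 339. This agrees with the protocol.

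The arithmetic in section 2.5 is sound. The question is which analysis it belongs to.

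**Variance factor and power by analysis, 96 evaluable per arm.** SE = 27.9 × √(factor × 2/96); power from the noncentral t at two-sided 2.5%.

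| Analysis of T1 | Factor | SE | Power |
|---|---|---|---|
| Baseline as covariate | 1 − r² = 0.64 | 3.22 | 80.0% |
| Change from T0 | 2(1 − r) = 0.80 | 3.60 | 69.7% |
| T1 means, baseline ignored | 1.00 | 4.03 | 58.9% |

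The efficiency of change scores relative to the covariate analysis is 0.64/0.80 = 0.80, a loss of 20% of the evaluable sample.

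**Does the mixed model recover the loss?** The information matrix was computed for a mixed model with T0 as a response under compound symmetry, using the normal approximation:
- Arm-specific T0 means, 2 or 4 time points: SE 3.60, power 70.4%.
- The same, keeping the T0 values of all 113 per arm: SE 3.55, power 71.8%.
- T0 means constrained equal: SE 3.22, power 80.6%.

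The gain comes from the constraint or the covariate, not from using a mixed model.

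**Sample size needed for the change contrast.** 0.80 × 147.98 = 118.4, so 119 evaluable per arm. 119/0.85 gives 140 per arm, or 420 randomised. With an exact t-test it is 120 per arm; 120/0.85 gives 142 per arm, or 426.

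**Sensitivity to r (96 per arm, 2.5%, normal approximation).**

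| r | Change from T0 | Baseline covariate |
|---|---|---|
| 0.4 | 51.0% | 68.0% |
| 0.5 | 59.6% | 73.4% |
| 0.6 | 70.4% | 80.6% |
| 0.7 | 83.3% | 89.2% |

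The change contrast reaches the planned factor of 0.64 only when 2(1 − r) = 0.64, that is r = 0.68. At every r shown the covariate analysis is the stronger.

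**Size of the over-correction.** The standard error of the T0 difference is 4.03 with 96 per arm. A chance imbalance of that size moves the change-score estimate by (1 − 0.6) × 4.03 = 1.6 points relative to the adjusted estimate.

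**The case against.** The best defence is that section 2.10 omits baseline adjustment without ruling it out. Its list of model terms is not declared complete, section 2.5 speaks of baseline as a covariate in the regression model, and a condensed article may leave full parameterisation to documents not shown. A change-from-baseline outcome is also compatible with adjustment, since regressing change on group with baseline as covariate gives the same treatment estimate and SE as adjusting the T1 score. T0 as reference time would fit a model with a common baseline mean as well.

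Part of this stands: the 70% depends on reading section 2.10 as written, and either of those models would restore the planned power. But the finding does not rest on silence. Sections 2.9 and 2.10 name the outcome, the covariates and the reference time, and together these describe an unconstrained change contrast. The rescuing readings need words that are not there. In section 2.5 the covariate appears only to justify N.

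A second point is that section 2.10 sets a 5% level, at which the change contrast has 78.9% power, close to the target. This is correct arithmetic, but it drops the allowance for two comparisons on which the 80% was calculated, and the conflict between the two levels needs its own resolution. At 5% the covariate analysis would have 87.0%, so the loss from the choice of estimator remains.

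Finally, under randomisation the change-score estimate is unbiased and its type I error is intact. That is true. The cost is in power and in sensitivity to chance imbalance, not validity.

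**Conclusion.** The point holds. Followed as written, section 2.10 gives about 70% power for each primary comparison (69.7% by the t-test; about 72% if the baseline values of drop-outs stay in the model), not the stated 80%. The chance of missing a true 10-point difference rises from 20% to about 30% per comparison. This rests on the protocol's own SD, correlation, 2.5% level and drop-out, with equal SDs at T0 and T1 and arm-specific T0 means. If the true correlation were 0.68 or more, the change contrast would reach the planned power, but the protocol assumes 0.6. Because it concerns the primary analysis and the basis for N, it should be corrected before outcome data are examined.

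**What to change.** Keep N at 339 and amend the analysis text. In section 2.10, define the primary analysis as one of the following:
- a mixed model for repeated measures on the post-baseline FCRI scores (T1, T2, T3), with group, time, group by time, baseline FCRI, baseline by time and the three stratification factors; or
- a constrained longitudinal model with T0 as a response, one common T0 mean for all arms, and the stratification factors.

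Name the baseline-adjusted between-group difference at T1 as the primary estimate for each comparison with the wait-list, and reword section 2.9 to match. Change from baseline can still be reported descriptively.

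The cost is wording only. FCRI is already measured at T0 before randomisation (section 2.2, Table 3), and no procedure or recruitment target changes. With 82 of 339 participants included by 31 July 2025, the estimator can still be fixed in a dated amendment well before recruitment is due to finish. Retaining the change contrast at the 2.5% level and 80% power would instead require about 420 randomised participants.

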**Figure 2 brainsci-15-00900-f002:**
[figure not shown]
Head, torso, and hand acupressure points involved in the application of EFT (Figure adapted from Church et al. [29]). The process starts with a ‘Setup Statement’ while performing acupoint tapping on the side of the hand. For the remainder of the process, patients gently tap with two fingers on head and torso points while repeating the ‘Reminder Phrase’.

**Table 1 brainsci-15-00900-t001:** Secondary and tertiary objectives.

Secondary objectives
• Explore whether iEFT is more effective than iMMI for improving FCR
• Compare the efficacy of the two interventions relative to a WLC group on distress, QoL and health status
• Explore whether iEFT is more effective than iMMI (active control condition) for improving distress, QoL and health status
• Prevalence and predictors of FCR in cancer survivors
• The magnitude of the interventions to reduce FCR in cancer survivors
• The level of preference of the WLC group to (optionally) complete a course of iEFT or iMMI
• The level of efficacy of both interventions between younger and older cancer survivors (< or ≥50 years)
• The level of the efficacy of both interventions between cancer survivors participating within 1 year after ending curative therapy and cancer survivors participating ≥1 year after ending curative therapy
• The time spent by iEFT and iMMI practitioners (time toxicity per patient)
Tertiary objective *
• The effect of iEFT and iMMI on chronic biological stress measured as hair cortisol concentration.

* This objective will only be completed when the primary objective is positive.

**Table 2 brainsci-15-00900-t002:** Inclusion and exclusion criteria.

Inclusion criteria
• Minimum age of 18 years at the time of enrolment
• Dutch as main language
• Histologically confirmed diagnosis of a solid cancer or haematological malignancy
• Curative surgery, chemotherapy, radiation therapy, immunotherapy, hormone therapy, targeted drug therapy or a combination of these was completed at least 2 months ago and no longer than 5 years ago at the time of enrolment. *
• Expected life expectancy of at least 5 years
• Disease-free at the time of enrolment, as defined by the absence of somatic disease activity parameters
• High FCR based on the Cancer Worry Scale 6-item version [26] (cut-off ≥ 10)
• Sufficient mental and physical functional status
Exclusion criteria
• Treatment with palliative intent
• Mental deterioration

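### The two primary T1 contrasts are sized at a two-sided 2.5% level each, but the analysis section states only a 5% level and no multiplicity rule, and the two are not reconciled

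*Protocol article*

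**What the plan says.** Section 2.9 of the protocol article names two primary outcome measures. One is "The difference in mean scores from the baseline on the FCRI between the iEFT group and the WLC group at T1"; the other is the same contrast for iMMI, "The difference in mean scores from the baseline on the FCRI between the iMMI group and the WLC group at T1". Section 2.1 states them as two separate hypotheses.

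Section 2.5 computes the sample size for a 10-point difference with 80% power "at the two-sided 2.5% significance level (two experimental groups are compared against a single control").

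Section 2.10 describes linear mixed models with a time-by-group interaction and the stratification variables. It then says "Estimated marginal means with 95% confidence interval (CI) will be calculated for each time point for both groups", followed directly by "A 5% significance level will be used". The next paragraph adds: "Between-group differences in the primary outcome at the primary endpoint T1 will be further examined with pairwise comparisons with T0 as the reference time point". That paragraph states no level, and nothing in the section mentions Bonferroni, Holm, Dunnett, an order of testing, or an overall error rate.

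**The concern.** The parenthesis in 2.5 shows that the authors recognised the multiplicity problem and paid for it in sample size. The section that governs the analysis does not carry the decision over. An analyst who follows 2.10 would naturally judge each primary contrast at 5%; one who follows 2.5 would use 2.5%. A p-value between 0.025 and 0.05 is then a positive primary result under one section and not under the other.

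The error rate over the pair is the relevant one. The Abstract and the Background both say that iEFT and/or iMMI could be taken into practice if effective, so either contrast alone can carry a claim. The level should be settled now: 82 of 339 participants had been included by 31 July 2025, and a level chosen after the results are known would weaken the primary conclusion.

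**Working it through.** **Inputs.** From 2.5: difference 10 points, SD 27.9, power 80%, two-sided α = 0.025, baseline correlation r = 0.6, drop-out 15%. From 2.6: allocation 1:1:1.

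**1. Which level does the sample size rest on?** Per-group n = 2·SD²·(z₁₋α/₂ + z₀.₈)² / Δ².
- α = 0.025: 2 × 27.9² × (2.2414 + 0.8416)² / 10² = 147.98, so 148 per group and 444 in total, as stated.
- α = 0.05: 2 × 27.9² × (1.9600 + 0.8416)² / 10² = 122.2, so 123 per group and 369 in total, which does not match.

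The later steps also reproduce. 444 × (1 − 0.36) = 284.2, close to the stated 288 (96 per group), and 288 / 0.85 = 338.8, so 339. The design therefore rests on 2.5% per comparison; that figure is not a slip.

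**2. Family-wise error for the pair.** With equal arms and one shared control, the two test statistics have correlation 0.5. Under the global null (neither intervention has an effect), the two-sided error is 1 − P(|Z₁| < c, |Z₂| < c), and the error in the favourable direction is 1 − P(Z₁ < c, Z₂ < c), for bivariate normal Z.

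| Level per contrast | c | Any false positive, two-sided | False claim of benefit |
|---|---|---|---|
| 5% | 1.960 | 9.07% | 4.54% |
| 2.5% | 2.241 | 4.65% | 2.32% |

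A simulation of t-tests with 96 per group gave 9.0% and 4.6% for the two-sided column. If the tests were independent, the two-sided figures would be 9.75% and 4.94%; these are upper references only. Dunnett's adjustment, which uses the correlation, allows about 2.7% per contrast for 5% overall.

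**3. Power if 2.5% is used in the analysis, 96 evaluable per arm.**
- Adjusted for baseline FCRI (variance factor 1 − r² = 0.64): SE = 27.9 × √(0.64 × 2/96) = 3.22 and 10/3.22 = 3.10. The normal approximation gives power 80.6% at 2.5% and 87.4% at 5%; the t distribution gives 80.0% and 87.0%.
- Plain change from T0 without that adjustment (equal variances assumed, factor 2(1 − r) = 0.80): SE = 27.9 × √(0.80 × 2/96) = 3.60 and 10/3.60 = 2.78. Power at 2.5% is about 70%.

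**The case against.** The strongest reply is that 2.10 need not mean 5% for each contrast. The sentence closes the paragraph on the mixed models and the interaction. The T1 pairwise comparisons come in the next paragraph, which gives no level. An overall 5%, split as 2.5 explains, fits both sections. So does an interaction test at 5% that must succeed before the pairwise tests; as an illustration, a strict omnibus test at T1 as a gate would bring the error to about 4.1%. This stands in part. The text states neither reading, but it does not say outright that the split has been abandoned. A reader might infer that the primary contrasts will certainly be tested at 5% each with a 9% error rate. The documents support only the conditional statement.

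A reader might also infer that 95% intervals are specified for the primary contrasts. They are not. The 95% intervals in 2.10 are for estimated group means at each time point, which does not conflict with a 2.5% test of a difference. No interval level is given for the between-group differences.

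The 9.1% counts significant results in either direction. For the harm that matters most, adoption of an ineffective intervention, the matching figures are 4.5% and 2.3%. The ratio is about two either way.

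Finally, the article condenses a fuller protocol that is not shown and may settle the matter. That would excuse an omission. Here, two levels are printed for the same tests with nothing to connect them.

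**Conclusion.** The inconsistency is real and concerns the primary decision rule. Section 2.5 fixes 2.5% per contrast, and the sample size reproduces only at that level; section 2.10 gives 5% without qualification.

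If 5% is applied to each contrast, family-wise error is about 9.1% two-sided, against about 4.6% at the design level. This assumes that neither intervention has an effect, that the arms are equal in size and that no gate applies.

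Holding the analysis to 2.5% keeps the planned 80% power only if baseline FCRI is adjusted for. Section 2.10 names the stratification variables and uses T0 as the reference time point, but does not name baseline FCRI as a covariate, so the condition should be made explicit.

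A separate, minor point of consistency: the secondary list in 2.9 repeats the iMMI–WLC contrast without a time point ("health status;The difference in mean scores from the baseline on the FCRI between the iMMI group and the WLC group"), while the Table 1 objective "Explore whether iEFT is more effective than iMMI for improving FCR" has no entry there. This does not change the primary error rate. One might infer that the repeated line is a misprint for iEFT versus iMMI at T1. However, the line may refer to later time points, and Table 1 gives no time point for that comparison.

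**What to change.** In 2.10, state that each of the two primary T1 contrasts (iEFT–WLC and iMMI–WLC) is tested at two-sided 2.5%, with a 97.5% confidence interval for the between-group difference. Holm or Dunnett within the pair at 5% overall is an acceptable alternative. State that the unadjusted 5% level applies to the secondary outcomes. If the sponsor instead intends the interaction test to act as a gate, the section must say so and give the rule.

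In the same place, confirm that the primary analysis adjusts for baseline FCRI, as 2.5 assumes.

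Separately, ask the sponsor to reconcile the repeated iMMI–WLC line in 2.9 with the iEFT versus iMMI objective in Table 1, and to give the time point meant.

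The cost is wording only, to be settled before any comparative results are seen. The sample size stays at 339. Relative to testing each contrast at 5%, power falls from about 87% to the planned 80%.
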